### Study design

The CASP intervention will be tested in the form of a 1:1 non-randomized, controlled pilot study. The pilot study will consist of two arms, comparing the CASP intervention in the two districts of Balod and Rajnandgaon against Enhanced Usual Care in the two districts of Mungeli and Balodabazar.

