### Sample size

Since the present study is a pilot study (focused primarily on understanding feasibility and refining processes in anticipation of a full-scale trial), the sample size calculation is based on a conservative assumed rate of the secondary outcome (change in suicide attempts) of 10% at the end of 12 months in the control group. Thus, a minimum enrolment of 500 participants (250 control; 250 intervention) has a power of 80% (at a 2-sided alpha level of 0.05) to detect an absolute risk reduction of 10 percent points (minimal detectable difference of 10% between the groups (intervention and control), while allowing for an expected 20% loss to follow-up over the 12 months follow-up period.

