### Data analysis

*Implementation outcomes*

Descriptive statistics (means, medians and standard deviations) of the reach, adoption and implementation metrics will be calculated. Qualitative thematic analysis
^
27
^ of the in-depth interviews exploring feasibility and acceptability will be carried out using a mix of inductive and deductive approaches. Two coders will independently review transcripts, generate initial codes, and collaboratively develop a comprehensive codebook (initial coding). This will be followed by a pilot coding phase to ensure procedural consistency before independent coding of the remaining transcripts, with discrepancies resolved through consensus or third-rater consultation. Researchers will then interpret and refine final themes. Coding will be done using NVivo 1.4.1.

*Clinical outcomes*
1.Difference in percentage of re-attempted suicide and death by suicide

We will analyze the difference between the intervention and control group in the percentage of participants who, after initial visit in the hospital for a suicide attempt, have re-attempted suicide (including deaths by suicide) at 6 and 12 months of follow-up. For statistical analysis, we will use Bayesian binominal testing as implemented in the open software program JASP.
^
28
^ Bayesian analysis allows us to not only test whether the null hypothesis is true or false, but also to test how likely the alternative hypothesis (that the change in suicide rates between intervention and control) is given the data.
^
29,
30
^
2.Change in depression, suicide risk and TiC-P scores

The mean change in depression and suicidal behavior scores between baseline and 6-
and 12-
months follow-up within the intervention group will be calculated using Bayesian linear mixed models as implemented in JASP. Models will be estimated both with and without a random effect for location, to see if it is needed to control for any clustering effect.
^
31
^
3.Quality of life

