### Potential harms

Any untoward medical occurrence, and/or (b) serious adverse events: suicide attempt, death due to suicide, death due to other causes, violence experienced by the participant, violence experienced by any other family member, and unplanned hospitalization will be reported. Although suicide attempt and death by suicides are outcome variables, we will also monitor them as if they are serious adverse events to ensure that the intervention is not associated with increase in suicide/attempted suicides.

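### The Bayesian re-attempt test is described as showing whether the null is true, which a Bayes factor cannot do, and the stated 80% power belongs to a different, frequentist test

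*Protocol article*

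**What the plan says.** Under Data analysis, Clinical outcomes, item 1, the protocol article compares the percentage of participants who re-attempt suicide, deaths included, between arms at 6 and 12 months, using a Bayesian binomial test in JASP. It justifies the choice by saying that "Bayesian analysis allows us to not only test whether the null hypothesis is true or false", and adds that the method also tells how likely the alternative is given the data.

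The Sample size section is framed differently. It assumes a control-arm rate of 10% at 12 months and then claims that the planned 250 per arm "has a power of 80% (at a 2-sided alpha level of 0.05"). The target effect is worded as follows: "to detect an absolute risk reduction of 10 percent points". A loss to follow-up of 20% is built in.

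Potential harms says separately that attempts and suicides will be monitored as if they were serious adverse events, "to ensure that the intervention is not associated with increase in suicide/attempted suicides". It names no analysis for this.

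The design is a "1:1 non-randomized, controlled pilot study" with two districts per arm, and re-attempt is a secondary outcome.

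**The concern.** Two statements do not fit the method.

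First, a Bayes factor compares how well two models predicted the data. A value favouring the null says that the null did better than the particular alternative it was set against. It does not show that the null is true, and it does not say how large a difference remains compatible with the data. With few events, a diffuse alternative is penalised heavily, so the null can be favoured while a substantial increase or decrease is still open.

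Second, power and a two-sided alpha are properties of a rejection rule at the 5% level. The test to be run has no such rule, so the 80% tells the reader nothing definite about how often it will find the design difference.

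What is at stake is how a secondary but serious outcome is reported. An ambiguous result on suicide re-attempts could be written up as support for no difference, under wording that the protocol itself supplies.

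**Working it through.** **Inputs.** From Sample size: 250 enrolled per arm, 20% loss, so 250 × 0.8 = 200 evaluable per arm; control rate 10%; two-sided 0.05; power 80%. Assumptions, because the article gives none of these: the prior, a Bayes-factor threshold of 3, and the true rates of 15% v 10% used as an illustration. Clustering by district is ignored.

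**The plan's own figure.** The usual formula with pooled variance is n = [1.96√(2p̄(1−p̄)) + 0.842√(p₁(1−p₁) + p₂(1−p₂))]² / (p₁−p₂)².
- 10% v 0%, the literal reading of a 10-point reduction from 10%: 74 per arm, or 93 after dividing by 0.8. This does not give 250.
- 20% v 10%: 199 per arm, and 199/0.8 = 249. This gives the stated 250, and power at 200 per arm is 80.2%.

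The stated size therefore corresponds to a frequentist test of 20% v 10%. That the 10% base rate does not fit is a separate matter; here 20% v 10% serves as the pair at which the 80% is correct.

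**Bayes factors.** With x and y events in n = 200 per arm and flat Beta(1,1) priors, the factor in favour of the null is BF01 = B(x+y+1, 2n−x−y+1) / [B(x+1, n−x+1) · B(y+1, n−y+1)], and BF10 = 1/BF01. For a normal prior with standard deviation s on the log odds ratio, a normal approximation with sampling variance v gives BF01 = √((v+s²)/v) · exp{−½·L²·(1/v − 1/(v+s²))}, where L is the observed log odds ratio. Probabilities come from exact enumeration over the two binomials.

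| True rates | Two-sided 5% z test rejects | Bayes-factor event | Flat | N(0,1) | N(0, SD 0.5) |
|---|---|---|---|---|---|
| 15% v 10% | 32.6% | BF01 > 3 (for the null) | 57% | 15% | 0% |
| 20% v 10% | 81% | BF10 > 3 (for a difference) | 57% | 69–71% | 73–74% |

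The ranges in the last row reflect the numerical approximation used.

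The 0% has a simple cause. At equal observed rates of 10%, v = 2(1/20 + 1/180) = 0.111. The factor for the null is then √(1 + 0.25/0.111) = 1.8 with SD 0.5, and √(1 + 1/0.111) = 3.2 with SD 1. Under the narrower prior, even identical rates cannot pass the threshold.

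**A single result.** Suppose 30/200 re-attempt under CASP and 20/200 under control.
- Flat priors: BF01 is about 3.9 in favour of no difference.
- Normal priors: L = ln(30·180/(170·20)) = 0.463 and v = 1/30 + 1/170 + 1/20 + 1/180 = 0.095, giving BF01 of about 1.2 (SD 1) and 0.8 (SD 0.5).
- Interval: the standard error is √(0.15·0.85/200 + 0.10·0.90/200) = 0.033, so 5.0 ± 1.96 × 3.3 gives −1.5 to +11.5 points.
- Probability that the difference exceeds zero: about Φ(0.05/0.033) = 0.93.

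The same data can thus be read as moderate support for no difference or as no evidence either way, depending on the prior. The interval shows directly that an increase of about 11 points is not excluded.

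**Equal observed rates.** At 10% in both arms the half-width is 1.96 × √(2·0.1·0.9/200) = 5.9 points.

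**The case against.** The strongest reply is that a Bayes factor can legitimately weigh evidence for a null; that the sentence goes on to promise the plausibility of the alternative; and that the prior, threshold and any interval are ordinary content for an analysis plan that is not shown. Most of this stands. The missing prior and threshold are not faults here, nothing in the article rules out a credible interval, and the rate of favouring the null runs from 0% to 57% according to a prior that had to be assumed. What remains is what the article does state: that the test can settle whether the null is true, and that its power is 80% at 0.05.

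Four stronger readings are tempting and are not supported:
- **That the re-attempt test is the planned basis for a no-increase safety claim.** Potential harms describes monitoring of serious adverse events. It does not refer to the Bayesian test, and the Data analysis section does not mention safety.
- **That the plan misses a 5-point harm two times in three.** That figure (100% − 32.6% = 67.4%) belongs to a two-sided 5% z test that is not planned, and the 5-point harm appears nowhere in the documents.
- **That a null result could wrongly block a definitive trial.** The Progression criteria (Table 2 and the traffic-light rule) use recruitment, retention and qualitative feasibility and acceptability, not re-attempts.
- **That this is the only comparison between arms.** The cost-utility analysis also compares them; the statement holds only for re-attempts.

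**Conclusion.** The point holds as a correction of two statements. The true-or-false wording claims more than a Bayes factor can deliver. The power statement does not describe the analysis to be run: at the pair of rates where a 5% test has 81% power, the chance of a Bayes factor above 3 for a difference is between about 57% and 74% across three priors. How often the null would be favoured wrongly cannot be fixed from the documents, and the 0% to 57% range at 15% v 10% is itself the reason to report an interval. These figures rest on 200 evaluable per arm, a threshold of 3, the assumed priors and no clustering. Because the outcome is secondary and the study is a pilot, this is a modest but worthwhile change.

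**What to change.** - **Data analysis, Clinical outcomes, item 1:** make the reported result the posterior risk difference with its 95% credible interval and the probability that the difference exceeds zero. Delete the wording that the test shows the null to be true. A Bayes factor may stay as a supplement, described as relative evidence under a stated prior.
- **Sample size:** tie the stated alpha and power to that 95% interval excluding zero, or restate the power for the Bayesian decision rule.
- **Potential harms:** no harm margin is required. If a statement is made that CASP is not associated with an increase, report beside it the largest increase that the interval does not exclude, which is about 6 points if both observed rates are 10% with 200 per arm.

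The cost is a few sentences and one extra posterior summary, with no new data. The downside is a more modest statement about re-attempts. The wording should be settled before the comparative data are examined.

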### Participants

We will recruit adults (≥18 years of age), who present to emergency public health facilities (district hospitals, primary or community health centers) in Balod and Rajnandgaon districts with attempted suicide or are already admitted for attempted suicide within one week of the study start date. We will exclude individuals who are unable to communicate clearly due to medical conditions or speech/hearing disabilities despite reasonable accommodations, those unable to comprehend one of the local languages used by CHOs to deliver the intervention, and individuals who do not reside within the catchment area of Balod and Rajnandgaon Health and Wellness Centers (where trained CHOs are placed).

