Referrals to social benefits: Many suicides occur spontaneously in periods of crisis where there is a breakdown in coping mechanisms for life stressors, such as financial difficulties, sudden illness or managing a chronic illness, relationship difficulties, etc. According to the National Crime Records Bureau (2022), family issues and illness are the main contributors to suicide in India, accounting for 32% and 18% of all suicides in 2022 respectively, while ‘Unemployment’ accounted for 1.9% and ‘Bankruptcy or indebtedness’ accounts for 4.1% suicides.
^
4
^ Thus, increasing access to state provided social benefits and schemes which focus on unemployment and livelihood support can help address some of these risk factors. CHOs will be trained to refer individuals in need of social security and support (e.g., government-provided employment or pension benefits, disability schemes, etc.) to the appropriate government workers, and all CHOs will have a list of locally available schemes and programs which they can use to match people to schemes and provide further information during visits.

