**Cost** will be assessed from the health system (costs required to run the program), patient (healthcare expenses, quality of life), and societal (e.g. productivity losses) perspectives with a sub-sample of participants from the main participant pool in both arms. The sub-sample will be selected using a simple random number generator, ensuring every participant in the main sample has an equal probability of inclusion and minimizing selection bias. If a participant has been selected as part of the cost sub-sample, the cost data will be collected along with the rest of the study data that is relevant at that timepoint.

The health system costs will be stratified based on the agencies incurring the cost and the nature of the cost (start-up capital cost and recurrent costs). The random sub-sample of participants in the intervention and control groups (n=100, 25 per district) will be asked about their
**medical costs and productivity losses** in the previous four weeks using a modified Treatment Inventory of Costs in Patients (TIC-P) (Hindi)
^
22
^ at baseline and at 6 months follow up.

The TiC-P is a reliable instrument for collecting data on healthcare utilization and productivity loss in patients with mental health problems.
^
22
^
**Quality of life** will be assessed using the Hindi EuroQol-5D-5L (EQ-5D-5L) at baseline and at 6 months follow up. The EQ-5D-5L is a quality-of-life measure which has been widely used in India.
^
23
^ It measures quality of life via five dimensions, namely mobility, self-care, usual activities, pain/discomfort and anxiety/depression. Each dimension is measured by a Likert scale containing five levels spanning from a no problem to an extreme problem level.

*Secondary outcome measures*
1.Suicidal behavior

A modified Hindi version of the Columbia Suicide Severity Rating Scale (C-SSRS) Modified Screener Version
^
24
^ will measure suicidal behavior (suicidal intention, ideation, planning and fatal and non-fatal suicide attempt) at baseline and 6-
and 12-

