month follow up. The Modified C- SSRS Screener is a semi-structured tool which measures the risk of suicide by inquiring about suicidal behaviour in the person’s lifetime (baseline) and since the last contact point (follow up). The screener consists of 6 questions and can be completed in a few minutes. For the purposes of this study, a lifetime measure was added to the screener to collect data on previous history of suicide ideation and behaviour at baseline. Specifically, the tool explores:
1.The presence of thoughts about suicide (suicidal ideation),2.Actions taken by the individual, in relation to preparing for suicide,3.Instances when the person has either attempted suicide or initiated a suicide attempt that was interrupted by another person or halted voluntarily, and the timing of this (lifetime, since last contact).

The C-SSRS has been translated in over 60 countries (including Hindi, and in India) and takes approximately 5 minutes to complete when administered as a clinical interview. The scale can be used by non-specialists across a range of settings, including healthcare settings.
2.Symptoms of depression

The Hindi Patient Health Questionnaire (PHQ-9)
^
25
^ assessment can be used as a screening tool as well as measures of symptom severity for depression. The nine-item PHQ-9 uses a 4-
point Likert-scale with items ranging from 0 (not at all) to 3 (nearly every day). The PHQ-9 has been validated, widely used, and found to be suitable for use in India.
^
26
^

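### A linear model of mean change in a C-SSRS score does not clearly answer the within-arm aim on suicidal behaviour

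*Protocol article*

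**What the plan says.** The Aims section of the protocol article lists, as a secondary aim, the preliminary impact on suicidal behaviour and depressive symptoms at 6 and 12 months within the intervention group. For that aim, Data analysis (Clinical outcomes, item 2) names as the quantity to be estimated "The mean change in depression and suicidal behavior scores". The change runs from baseline to each of the two follow-up assessments, in the intervention arm alone, and the stated method is a Bayesian linear mixed model fitted in JASP. One sentence and one model serve both the PHQ-9 and the C-SSRS.

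Outcomes (Secondary outcome measures) says of the modified C-SSRS screener that it "will measure suicidal behavior (suicidal intention, ideation, planning and fatal and non-fatal suicide attempt) at baseline and 6" months, with a further assessment at 12 months. On its format the article says: "The screener consists of 6 questions and can be completed in a few minutes". It lists thoughts, preparatory actions, and actual, interrupted or halted attempts with their timing. On the recall period, it describes the tool as "inquiring about suicidal behaviour in the person’s lifetime (baseline) and since the last contact point (follow up"). The PHQ-9, by contrast, is given a 0 to 3 grading per item and is called a measure of symptom severity.

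Under Participants, people are enrolled who present "with attempted suicide or are already admitted for attempted suicide within one week of the study start date". Item 1 of the clinical analyses separately compares the percentage who re-attempted, deaths by suicide included, between the two groups.

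**The concern.** A mean change is informative when the score is a graded quantity on which a fall has one meaning. The PHQ-9 is presented that way. The C-SSRS screener is presented as a set of presence questions that run from a thought to an attempt, and the construct also includes fatal attempts. A single mean has to combine these somehow.

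At stake is the only analysis planned for the within-arm aim on suicidal behaviour. The control group gets only a short re-attempt survey (Data collection), so no comparator would show how much of a fall in the score comes from its construction. A reported mean improvement could be read as less suicidal behaviour when the figure does not clearly carry that meaning.

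**Working it through.** The protocol gives no figure for this score, so there is none to reproduce. It also gives no scoring rule, so the two natural ones are examined as assumptions.

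**Inputs from the protocol article:** six questions; every participant enrolled after an attempt; lifetime recall at baseline and recall since last contact at follow-up; mean change by a linear mixed model.

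**Scoring A (assumed): one point per question, sum 0 to 6.**

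Let j be the number of the other five items positive at baseline and k the number at follow-up. The attempt item is 1 for everyone at baseline.

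- Participant who re-attempts: change = (1 + k) − (1 + j) = k − j. The attempt item cancels, and the score falls whenever k < j.
- Participant who does not re-attempt: change = (0 + k) − (1 + j) = k − j − 1. A re-attempt therefore weighs the same as any one other item.
- Starting from all six positive (j = 5): change = k − 5, which is −5, −4, −3, −2, −1 for k = 0 to 4, and 0 for k = 5.
- Over all pairs of answer patterns with the attempt item positive both times (2^5 × 2^5 = 1,024), the sum falls in (1,024 − 252)/2 = 386, or 38%; 252 is the number of pairs with equal sums. If three further ideation items are skipped when a gate item is negative, it falls in 125 of 324 (39%). These are counts of patterns, not probabilities for patients.
- Group level: take two possible follow-up results. In the second, re-attempts are 10 percentage points more frequent and each of the other five items is 10 points less frequent. The second mean differs by 0.10 − 5 × 0.10 = −0.40, so it looks better despite more re-attempts.
- The attempt item alone moves from 1.0 to the re-attempt proportion. With an assumed 5% to 20% re-attempting, it contributes 0.05 − 1 = −0.95 to 0.20 − 1 = −0.80 to the mean change.

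**Scoring B (assumed): highest level reported, with attempt at the top.**

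- Baseline equals the maximum for everyone, with SD 0.
- Change = follow-up level − maximum, so it is zero or negative. A participant who re-attempts scores 0.
- The mean change is then the follow-up mean shifted by a constant. Baseline adds no information, and the group cannot worsen.

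Equal recall windows would not remove either result, because any baseline window that includes the index attempt gives the same starting value.

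**Model fit (illustration only).** Assume 50%, 70% or 85% of follow-up sums are zero, with the remainder spread over 1 to 6 in proportions 0.35, 0.25, 0.12, 0.10, 0.08 and 0.10.

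| Assumed share at zero | Mean | SD | Skew | Fitted normal mass below 0 |
|---|---|---|---|---|
| 50% | 1.30 | 1.76 | 1.35 | 23% |
| 70% | 0.78 | 1.51 | 2.11 | 30% |
| 85% | 0.39 | 1.14 | 3.38 | 37% |

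**The case against.** The strongest reply is that the article states no scoring rule, and that a condensed article may leave one to the full protocol or analysis plan. That stands: the missing rule is not itself a fault. It also means that a reader should not infer that the plan will count people who re-attempt as improved. That follows only from a unit-weight sum. Under a highest-level score such a person changes by 0. The title of item 2 speaks of suicide risk, which fits a severity level at least as well as a sum. The drop from 6 to 1 is an extreme pattern. It needs no ideation, intent, plan or preparation reported over a whole follow-up interval. The remark under Study interventions that "Many suicides occur spontaneously in periods of crisis where there is a breakdown in coping mechanisms" is a rationale for social-benefit referrals and does not establish that pattern.

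A reader might also infer that re-attempts would be hidden inside the mean. They would not: item 1 analyses them as a percentage with deaths included, and Potential harms monitors them as serious adverse events.

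Nor do the documents support a claim that the normal model fails by a known amount. They give no score distribution, so the 23% to 37% belongs to the illustration. With roughly 200 to 250 participants, an estimated mean tolerates a good deal of skew. The article also uses the term linear mixed model loosely: under Quality of life it attaches a logit link and ordinal family to it. No such family is named for this score.

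What survives does not depend on choosing a scoring rule. Both natural rules leave a mean change that is hard to interpret.

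**Conclusion.** The point holds in a limited form. The protocol fixes a linear mean-change analysis for an instrument that it describes as six presence questions of unequal gravity. Under a sum, falls in other items can offset a re-attempt one for one. Under a highest-level score, all participants start at the ceiling and change is zero or downward by construction. Neither result clearly answers the within-arm aim on suicidal behaviour.

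The scope is one secondary, preliminary, intervention-only analysis in a pilot whose primary outcomes concern implementation. It enters no progression criterion, and the sample size is based on suicide attempts, not on this score. The conclusion rests on the two scoring rules as assumptions and on every participant having attempted before baseline, which the eligibility criteria make certain. The objection is to what the mean represents; lack of normality is a lesser matter.

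**What to change.** Keep the linear mixed model for the PHQ-9 only. For the C-SSRS in the intervention arm, replace the mean score change with:

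- (a) any ideation, and (b) any plan, intent or preparatory action, as separate yes/no outcomes at 6 and 12 months, each with a Bayesian logistic mixed model;
- (c) any attempt or death by suicide as a follow-up proportion, defined consistently with item 1 and not as change from baseline.

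If one summary is preferred, use the worst level reported (none < ideation < plan or intent < attempt or death) in a cumulative-logit mixed model. Apply it to the 6- and 12-month levels only. As a change from baseline it would meet the same ceiling as scoring B.

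The cost is a change of analysis wording. The same data are used, with no new visits or instruments, and the article says that data collection runs to November 2025. The downside is several results, or an ordinal odds ratio, in place of one mean change, and outcome (c) partly repeats item 1.

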## Protocol

### Aims

The primary aims of this study are to assess the feasibility, acceptability, reach, adoption and implementation (including cost) of delivering the CASP intervention within the public health system in Chhattisgarh.

The secondary aim is to assess:
•Difference in rate of suicide re-attempt at 6 and 12 month follow up between intervention and control groups,•Preliminary impact on suicidal behaviour and symptoms of depression at 6 and 12 month follow up within the intervention group only.

For the purposes of this study, suicidal behaviour is defined as inclusive of suicidal intention, ideation, planning and fatal or non-fatal suicide attempt.

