### Data collection

Baseline demographic data—including age, gender, education, marital status, employment status, caste/tribal background, income, and contact details—will be collected by Community Health Officers (CHOs) from consenting participants. Study records will include the following: (1) record books maintained by nurses at health facilities, documenting the date, age, gender, method of attempt, verbal consent status, and, if applicable, reasons for refusal; and (2) CHO records detailing the dates and locations of participant visits to monitor adherence to the CASP intervention schedule (at 1, 2, 4, 7, and 11 weeks post-attempt).

For outcome assessments, the Columbia-Suicide Severity Rating Scale (C-SSRS) and the Patient Health Questionnaire-9 (PHQ-9) will be administered to participants in the intervention group at baseline and during follow-ups at 6 and 12 months. Within the control arm, a brief follow up survey will be administered that captures suicide re-attempt at 6 and 12 month follow up points. Data collection will be conducted by trained data collectors, who are local Master’s graduates in mental health or related fields with prior experience in the health system.

To support the cost analysis and economic evaluation, a brief cost survey (Modified TiC-P) and the EuroQol-5D-5L will be administered to a random sample of 50 participants in both the intervention and control groups at baseline and at the 6-month follow-up. Data collection will be conducted using paper-and-pencil assessments or self-administered forms, based on participant preference.

Qualitative follow-up data will be collected through in-depth and semi-structured interviews, lasting approximately one hour each. These interviews will be conducted by research team members and audio recorded with prior informed consent for transcription purposes. Acceptability interviews with participants will include a random sample selected independently of intervention completion status, ensuring the inclusion of individuals who may have dropped out of the study. See
Figure 1 for research and data collection procedures.

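### The C-SSRS change score compares a lifetime baseline containing the index attempt with a shorter follow-up period, so it leans towards improvement even if CASP has no effect

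*Protocol article*

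**What the plan says.** All references are to the protocol article.

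- **Aims.** A secondary aim is "Preliminary impact on suicidal behaviour and symptoms of depression at 6 and 12 month follow up within the intervention group only". The construct is broad: "suicidal behaviour is defined as inclusive of suicidal intention, ideation, planning and fatal or non-fatal suicide attempt".
- **Participants.** Adults are enrolled if they present "with attempted suicide or are already admitted for attempted suicide within one week of the study start date".
- **Outcomes, secondary outcome measures.** The period covered by the modified C-SSRS screener is "lifetime (baseline) and since the last contact point (follow up". The section adds that "a lifetime measure was added to the screener to collect data on previous history of suicide ideation and behaviour at baseline".
- **Data collection.** The C-SSRS and PHQ-9 "will be administered to participants in the intervention group at baseline and during follow-ups at 6 and 12 months". In the control arm, "a brief follow up survey will be administered that captures suicide re-attempt at 6 and 12 month follow up points".
- **Data analysis, clinical outcomes, item 2.** The quantity to be estimated is "The mean change in depression and suicidal behavior scores between baseline" and each follow-up visit, in the intervention group, by Bayesian linear mixed models.
- **Data analysis, clinical outcomes, item 1.** Re-attempts after the initial hospital visit, including suicide deaths, are compared between arms at 6 and 12 months.

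The article does not align the two recall periods, take the index attempt out of the baseline score, or caution that the within-arm change cannot be attributed to CASP.

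**The concern.** A change score measures change in a person only if the same question is asked over the same length of time. Here the baseline question reaches back over a lifetime and the follow-up question over some months. Someone whose risk never altered would tend to score lower at follow-up, because there has been less time for anything to be counted.

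Entry adds a second push in the same direction. Attempt is part of the outcome, and a recent attempt is the reason for enrolment, so that component starts at its ceiling.

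With no C-SSRS series in controls, neither effect can be subtracted. A fall in the score could be published as early evidence that CASP reduces suicidal behaviour when part or all of it came from the way the score was built.

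**Working it through.** The plan gives no figure for the within-arm change, so there is none to reproduce. The check asks what the planned score would show if CASP did nothing.

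**Inputs**
- Attempt item at baseline: 100%, from the eligibility rule (Participants).
- Re-attempt rate with no effect: 10% at 12 months, the control-group assumption in Sample size. A range of 5% to 30% is my assumption.
- Evaluable participants: 250 × (1 − 0.20) = 200 (Sample size).

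**Step 1: the attempt item alone.** Fall = 1 − r, with 95% interval (1 − r) ± 1.96 × √(r(1 − r)/200). At r = 0.10: 0.90 ± 1.96 × √(0.09/200) = 0.90 ± 0.042.

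| Re-attempt rate r | Fall with no effect (points) | 95% interval |
|---|---|---|
| 5% | 95 | 92 to 98 |
| 10% | 90 | 86 to 94 |
| 20% | 80 | 74 to 86 |
| 30% | 70 | 64 to 76 |

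The 10% covers 12 months. If the 12-month visit asks only about the time since the 6-month visit, the follow-up figure is lower and the fall larger.

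**Step 2: the recall periods.** If p is the chance that an ideation or planning item is positive in one follow-up window, and risk is constant, the chance over a lifetime worth k windows is 1 − (1 − p)^k. This exceeds p whenever k > 1 and 0 < p < 1, so these items also fall with no effect.

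**Step 3: an illustrative total.** I assumed six items scored present or absent and summed. The attempt item is 1 at baseline and 10% at follow-up. The other five have per-window log-odds of 0, −0.4, −1, −1.4 and −1.8 plus a person effect with SD 1, constant over time. There were 500 simulated cohorts of 200. None of these item rates, nor the scoring, comes from the protocol.

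| Lifetime as multiple of follow-up window (k) | Mean change with no effect | Mean change / SD of change |
|---|---|---|
| 10 | −3.6 | −2.8 |
| 4 | −2.7 | −2.0 |
| 2 | −1.8 | −1.3 |
| 1 (matched, index attempt counted) | −0.9 | −0.7 |

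Every simulated cohort showed a nominally significant improvement. The last row needs no simulation: with matched windows the other five items cancel on average, leaving 0.10 − 1 = −0.90. Matching the windows therefore shrinks the artefact but does not remove it while the index attempt counts at baseline.

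**Step 4: PHQ-9.** No mismatch of recall period is stated, and eligibility fixes no PHQ-9 value. Recruitment & Retention has the health worker meet the participant within a week of discharge, so baseline appears to fall soon after a crisis. Natural recovery and regression to the mean would then lower later scores on average, but the score is free to rise.

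**The case against.** The strongest reply is that the lifetime-to-window score is partly an inference. The lifetime measure was added to record history, so the screener's own shorter window may survive at baseline and may be what enters the model. Scoring detail can properly sit in a document not shown. This has force on size: the totals in Step 3 are illustrations only. It does not remove the problem. The one statement of the recall periods is lifetime at baseline and since last contact at follow-up, and a recent baseline window would still contain the index attempt.

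A reader might also infer several stronger things that the documents do not support:

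- *The analysis cannot give an unfavourable answer.* Only the attempt component is fixed by eligibility. Ideation and planning are pushed downwards but not determined, and PHQ-9 can stay flat or worsen.
- *PHQ-9 shares the same flaw.* It has the ordinary weakness of an uncontrolled before-after comparison, which is milder.
- *The trial would report a 90-point improvement.* The plan does not analyse change in the attempt item alone. The figure shows direction and scale for one component.
- *There are no control data.* Re-attempt is collected in controls and compared between arms, counting only events after the index visit. That analysis is unaffected. Only C-SSRS and PHQ-9 scores lack a comparator, and Aims says so openly.
- *A linear model is wrong for yes/no items.* The article mentions six questions but does not give the response format.
- *The decision to proceed is at risk.* Progression criteria rest on recruitment, retention and qualitative feasibility. This outcome is secondary and labelled preliminary.

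**Conclusion.** The point holds for the C-SSRS. Followed as written, the planned change score is biased towards improvement with no CASP effect, through unequal recall periods and a baseline that includes the qualifying attempt. For the attempt component the fall is about 90 points at the protocol's 10% rate, and 70 to 95 points over an assumed 30% to 5%. The effect on a total score cannot be stated, because its construction is not given. That the index attempt counts at baseline is my reading of the eligibility rule together with the lifetime question.

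For PHQ-9 the conclusion is narrower: within-arm change is interpretable as description but not as an effect of CASP. The consequence is limited to a secondary outcome outside the progression criteria, but calling the result impact claims more than the design can give.

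**What to change.** 1. Do not use lifetime answers or the index attempt in any C-SSRS change score. Either report 6- and 12-month levels on a stated fixed window, or compute change only for ideation and planning items asked over the same recent window at each visit. If baseline forms recorded lifetime answers only, the first option is the one available.
2. Keep the lifetime answers as a description of history at entry.
3. Present within-arm C-SSRS and PHQ-9 change as descriptive. In Aims, replace the reference to preliminary impact with wording such as *change over time, not attributable to CASP*.
4. Rest the effectiveness signal on the between-arm re-attempt comparison in item 1 of the clinical outcomes. It remains a non-randomized comparison.

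This costs a change of analysis and wording, plus the notice to the two ethics boards and the registry that Protocol amendments requires. The downside is a weaker and less favourable statement about effect.

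Collecting C-SSRS and PHQ-9 at remaining control follow-ups is optional. Study status says data collection is under way, so some contacts may have passed. Controls have no baseline scores, so the comparison would be unadjusted for baseline severity as well as non-randomized. It would also add respondent time and change the outcomes, so it is not a clean remedy.
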